### Costs analysis

The costs of the procedures will be calculated by determining the amount of guiding catheters, regular wires, pressure wires, FD-OCT-catheters, balloon dilatation catheters, stents, antiplatelet therapy, adenosine, contrast media, and hospital days used for each patient’s procedure. These will be multiplied by the cost of each resource in Euros. Personnel and laboratory time costs will not be included because assumed to be similar between the two strategies.

Costs of repeated PCI without myocardial infarction, repeated PCI in the setting of a non peri-procedural myocardial infarction and coronary artery bypass grafting will be based on the Italian National Health System’s reimbursement rate per diagnosis-related group.

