### Sample size calculation for peri-procedural management costs

The costs for each arm are anticipated to be the combination of diagnostic procedural costs, interventional procedures (eventually derived from the diagnostic ones) and costs related to events occurring during the follow up. On the basis of the NASCI study, we expect a 30% of PCI in the FFR-guided arm [17]. Contrastingly, according to our experience (three years FD-OCT experience at our institution, unpublished data), PCI is anticipated to be performed in about 50% of the FD-OCT-guided arm. Thus considering the mean costs of a FFR-guided PCI (3600€ for PCI + 940€ for the pressure wire + 170€ for adenosine = 4710€) and of an FD-OCT guided PCI (3600€ for PCI + 1600€ for the FD-OCT catheter = 5200€) and the costs of a coronary angiography with FFR (500€ for coronary angiography + 940€ for the pressure wire plus 170€ for adenosine = 1610€) and of a coronary angiography with FD-OCT (500€ for coronary angiography + 1600€ for FD-OCT catheter = 2100€) we expect an overall costs reduction of 30% in the FFR-guidance group compared to the FD-OCT guidance group. Assuming no occurrence, or at least a similar occurrence of MACE, or recurrence of angina at 30 days follow up in both arms, we expect an overall 30% reduction of costs at 30 days follow up in the FFR-guided arm. A total number of 220 patients (110 randomized to FFR guidance and 110 to FD-OCT guidance) with an alpha error of 5% and a beta error of 20% has been calculated to be needed to test this hypothesis.

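### Staff and laboratory time is left out of the cost endpoint as similar in both arms, which conflicts with the plan's own expected PCI rates of 30% and about 50%

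*Protocol article*

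**What the plan says.** Global cost of each strategy at one and thirteen months is a secondary endpoint (Study endpoints) and has its own sample size of 220.

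- **Costs analysis, index procedure.** Cost is built from counts of devices, drugs, contrast and hospital days for each patient, multiplied by unit prices. One component is removed: "Personnel and laboratory time costs will not be included because assumed to be similar between the two strategies".
- **Costs analysis, follow-up.** A price source is named for repeated PCI with or without a non-peri-procedural infarction and for bypass surgery. The list opens with "Costs of repeated PCI without myocardial infarction", and the source is the national "reimbursement rate per diagnosis-related group".
- **Sample size calculation for peri-procedural management costs.** For one arm, "we expect a 30% of PCI in the FFR-guided arm"; for the other, "PCI is anticipated to be performed in about 50% of the FD-OCT-guided arm". The section also counts the costs of events during follow-up as part of each arm's cost.
- **Procedure description.** PCI may be done in the same session or staged as a second one.
- **FD-OCT guidance.** Major stent findings lead to further balloon or stent treatment. The centre's past FD-OCT procedures met those cutoffs in one third of cases.
- **Sample size calculation for clinical outcome.** The expected FD-OCT benefit is attributed to treating more stenoses and to optimising stenting.

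**The concern.** Leaving a cost component out is harmless to a between-arm difference only if its mean is equal in the two arms. The article gives equality as its reason, but elsewhere expects 20 percentage points more PCI in one arm. If a PCI occupies the room and staff longer than a diagnostic run, the omitted component depends on the arm. A staged PCI adds a whole second session. Devices and hospital days for that session can be counted under the stated rule, but its staff and room time cannot.

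A smaller matter lies in the same section. Read literally, the follow-up list prices only a PCI that repeats an earlier one. Deferred patients, expected to be 70% of the FFR arm and 50% of the FD-OCT arm, have no earlier study PCI to repeat. An analyst who follows the words strictly could leave their first PCI unpriced, and the share of such patients differs by arm.

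At stake is the accuracy of the euro difference between strategies. The economic comparison is one of the trial's stated aims.

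**Working it through.** **Inputs, all from the cost sample-size section unless noted**

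- PCI rates: 0.30 (FFR), 0.50 (FD-OCT).
- FFR-guided PCI: "3600€ for PCI + 940€ for the pressure wire + 170€ for adenosine = 4710" euros.
- FD-OCT-guided PCI: "3600€ for PCI + 1600€ for the FD-OCT catheter = 5200" euros.
- Angiography with FFR only: "500€ for coronary angiography + 940€ for the pressure wire plus 170€ for adenosine = 1610" euros.
- Angiography with FD-OCT only: 500 + 1,600 = 2,100 euros.
- Revascularization rate in lesions with FFR above 0.80: 3.2% (FD-OCT guidance, citing an earlier trial).
- Assumed, because the article gives no figure: x, the extra staff and room cost of a PCI over a diagnostic-only procedure, 300 to 1,000 euros.

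**Step 1. Reproduce the plan's figure.** Mean cost = PCI rate × PCI cost + (1 − PCI rate) × diagnostic cost.

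- FFR: 0.30 × 4,710 + 0.70 × 1,610 = 2,540 euros.
- FD-OCT: 0.50 × 5,200 + 0.50 × 2,100 = 3,650 euros.
- Difference: 1,110 euros; 1,110 / 3,650 = 30.4%. The stated 30% reproduces.

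**Step 2. Split the difference.** The step from diagnostic run to PCI costs 3,100 euros in both arms (4,710 − 1,610; 5,200 − 2,100).

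- PCI gap: 0.20 × 3,100 = 620 euros (56%).
- Dearer diagnostic device set: 2,100 − 1,610 = 490 euros (44%).

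**Step 3. Effect of the omitted time.** With equal diagnostic time in both arms, the omitted amount is (0.50 − 0.30) × x = 0.20x.

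| x (euros, assumed) | omitted, 0.20x | share of 1,110 | difference with time costed |
|---|---|---|---|
| 300 | 60 | 5.4% | 1,170 |
| 500 | 100 | 9.0% | 1,210 |
| 1,000 | 200 | 18.0% | 1,310 |

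**Step 4. What would cancel it.** If the FFR diagnostic step cost y euros more in time than the FD-OCT step, the omitted difference would be 0.20x − y. Exact cancellation needs y = 60 euros at x = 300 and y = 200 euros at x = 1,000. If the FD-OCT step takes longer, the omission grows.

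**Step 5. The literal gap in follow-up pricing.** Let q be the share of deferred patients who later have a first PCI, taken as equal in both arms, at 3,600 euros each. The unpriced amount is 0.70 × q × 3,600 in the FFR arm and 0.50 × q × 3,600 in the FD-OCT arm. At q = 0.032 these are 80.64 and 57.60 euros, so FFR cost would be understated by 23 euros more than FD-OCT cost (23 / 1,110 = 2.1%). This runs against the effect in Step 3.

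**Step 6. Both together at 13 months.** Difference = 1,110 + 0.20x − 23. This is 1,147 euros at x = 300 and 1,287 euros at x = 1,000. FFR stays cheaper throughout.

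**The case against.** There is a fair case on the other side, and much of it stands.

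- **The direction is conservative.** Leaving out staff time works against the hypothesised FFR saving. The cost sample size also concerns 30 days, when later first PCI hardly counts. Both points hold. They limit the consequence but do not make the stated reason consistent with the expected PCI rates.
- **Diagnostic times might offset.** Inducing hyperaemia takes time, and the FFR arm also has optimisation after stenting. An offset is possible, but the article claims none and gives no times.
- **Repeated may be loose wording.** The section on clinical outcome measures speaks of repeat revascularization after follow-up angiography without excepting deferred patients, and the cost sample-size section includes follow-up event costs. A reader might infer that a first PCI in a deferred patient is excluded from cost. The article does not say so; it leaves a gap on the literal text, and a small one.
- **The PCI gap is not the whole difference.** A reader might infer that the entire expected saving rests on PCI rates. Step 2 shows that 490 of 1,110 euros would remain at equal rates.
- **Two valuation bases.** A reader might call it an error to cost index procedures by resources and later ones by tariff. This is an openly stated choice of method, and nothing in the article makes it wrong.

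**Conclusion.** The assumption of similar staff and laboratory time conflicts with the plan's own expectations of PCI use and should not stand as the reason for the exclusion. Under equal diagnostic times, the planned costing understates the FD-OCT minus FFR difference by 0.20x per patient: 60 to 200 euros, or 5% to 18% of 1,110, for an assumed x of 300 to 1,000 euros. The size rests wholly on that assumption and on the planned PCI rates being realised. The article also does not say what its 3,600 euros per PCI contains.

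A reader might go further and infer that the cost endpoint is biased in a known direction at 13 months, or that the economic conclusion could turn. The documents support neither. The two omissions oppose each other (at q = 3.2% they cancel at x of about 115 euros, since 23 / 0.20 = 115), diagnostic times are unknown, and FFR remains cheaper over the ranges shown. This is a point about the accuracy of a secondary endpoint. It is worth correcting because correction is cheap.

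**What to change.** 1. In Costs analysis, remove the statement that personnel and laboratory time is similar. Cost it per session, including staged sessions, from recorded procedure times and one unit cost per hour.
2. If times were not recorded, prespecify a sensitivity analysis instead. Add a time cost per PCI and a time cost per diagnostic procedure, the latter allowed to differ between FFR and FD-OCT, and report the cost difference over a stated range of both.
3. Replace repeated PCI in the follow-up list with any PCI or bypass after the index strategy, with staged PCI counted as index. A first PCI in a deferred patient is then priced, in line with the inclusion of follow-up event costs in the sample-size section.

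**Cost.** Item 1 needs some extra data extraction and one unit cost. The article does not say whether procedure times are kept, and recruitment began in April 2013, so times for patients already treated may have to be retrieved. Item 2 can be run from the number of procedures per patient plus assumed unit costs. Item 3 is a change of wording. None of these alters patient management or the sample size.

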### Sample size calculation for clinical outcome

FFR-based treatment has proven to be superior to standard (based on angiography only) treatment by reducing the occurrence of MACE in the long-term [35]. Yet angina relief (an important determinant of quality of life in patients with ischemic heart disease) was not ameliorated by FFR guidance in a recent trial [7]. Thus, the FORZA trial aims to test if FD-OCT guidance may help to improve the clinical management of patients with ischemic heart disease and inconclusive results at coronary angiography. Since hard clinical endpoints are expected to have low frequency and PCI (especially in patients with good prognosis) is performed with the aim of improving the quality of life by eliminating angina and improving heart function, the occurrence of significant residual angina (<90 score at SAQ angina frequency scale) at 13 months has been considered as the primary endpoint.

For sample size calculations, we focused our attention on the clinical outcome at 13 months (a timepoint chosen assuming that most of patients had completed their 12-month double antiplatelet therapy one month before). Then, based on the FAME trial [7], we anticipate 20% of patients will be suffering from persistent angina at follow up in the FFR guidance group. Thus, 20% of patients are expected to have reached the primary endpoint at 13 months in the FFR guidance group. For the present study, we hypothesize that FD-OCT guidance could be able (due to the treatment of a greater number of stenoses and the optimization of stenting procedures which may reduce the rate of untreated angina-causing lesions) to reduce the occurrence of the primary endpoint by 50%. As a consequence, a total number of 400 patients (200 randomized to FFR guidance and 200 to FD-OCT guidance) has been calculated to be needed with an alpha error of 5% and a beta error of 20%.

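### Personnel and laboratory time is left out of the costs as similar in both arms, although the plan expects PCI in about 50% versus 30% of patients; the absolute cost difference is probably understated

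*Protocol article*

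**What the plan says.** The Costs analysis section builds each patient's procedure cost from itemised devices and from "stents, antiplatelet therapy, adenosine, contrast media, and hospital days used for each patient’s procedure", each multiplied by a unit price in euros. Staff and room time is excluded, and one reason is given: "Personnel and laboratory time costs will not be included because assumed to be similar between the two strategies". Later revascularisations are priced at national reimbursement rates.

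The section on sample size for peri-procedural management costs gives the PCI rates used for planning: "we expect a 30% of PCI in the FFR-guided arm", while "PCI is anticipated to be performed in about 50% of the FD-OCT-guided arm". From these rates and four unit costs it expects costs 30% lower with FFR.

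The section on sample size for clinical outcome bases the expected benefit of FD-OCT partly on more treatment, namely "due to the treatment of a greater number of stenoses and the optimization of stenting procedures". The Procedure description section allows PCI in the same session or in a second, staged one. Under Study endpoints, global strategy cost at one and thirteen months is a further secondary endpoint.

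**The concern.** The exclusion would be harmless for the absolute difference if the omitted cost were equal in the two arms. The plan's own PCI rates argue against that. A patient who goes on to PCI uses room and staff time that a patient who has only the measurement does not, and the plan expects 20 more such patients per 100 under FD-OCT. A cost that rises with the number of PCIs is therefore dropped on a premise that the plan's figures contradict.

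At stake is the euro difference between strategies at one and thirteen months. The omission concerns the index procedure, so it is present even if no follow-up event occurs. Comparing costs is a declared aim of the trial, so the reason for leaving a component out should agree with the plan's other assumptions.

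**Working it through.** **Inputs from the cost sample size section.**
- PCI rate: 0.30 (FFR), 0.50 (FD-OCT).
- FFR with PCI: "3600€ for PCI + 940€ for the pressure wire + 170€ for adenosine = 4710" EUR. FFR without PCI: "500€ for coronary angiography + 940€ for the pressure wire plus 170€ for adenosine = 1610" EUR.
- FD-OCT with PCI: "3600€ for PCI + 1600€ for the FD-OCT catheter = 5200" EUR. FD-OCT without PCI: 500 + 1600 = 2100 EUR.

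**Step 1: the plan's own figure.** Expected cost = PCI rate × cost with PCI + (1 − PCI rate) × cost without PCI.
- FFR: 0.30 × 4710 + 0.70 × 1610 = 2540 EUR.
- FD-OCT: 0.50 × 5200 + 0.50 × 2100 = 3650 EUR.
- Difference: 1110 EUR; 1110 / 3650 = 30.4%. The stated 30% is reproduced.

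**Step 2: where the 1110 EUR comes from.** PCI adds 3100 EUR in either arm (4710 − 1610 = 5200 − 2100).
- PCI-rate gap: 0.20 × 3100 = 620 EUR.
- Device and drug costs: 2100 − 1610 = 490 EUR.

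More than half of the planned difference is thus due to the PCI rate, the same quantity that drives the omitted time.

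**Step 3: the omitted time cost in euros.** Let each PCI add t EUR of room and staff time, the same in both arms. The rule drops 0.30t per FFR patient and 0.50t per FD-OCT patient, a gap of 0.20t. The documents give no t. Assume 30 to 60 extra minutes per PCI and 5 to 20 EUR per minute:
- Low: t = 30 × 5 = 150 EUR; gap 0.20 × 150 = 30 EUR (30 / 1110 = 2.7%).
- High: t = 60 × 20 = 1200 EUR; gap 0.20 × 1200 = 240 EUR (240 / 1110 = 21.6%).

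**Step 4: what would cancel it.** FFR assessment would have to take longer than FD-OCT assessment by 0.20 × the PCI time, averaged over all patients: 0.20 × 30 = 6 minutes to 0.20 × 60 = 12 minutes.

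**Step 5: the relative saving.** Let c be a time cost common to every patient in both arms. The relative saving becomes (1110 + 0.20t) / (3650 + c + 0.50t).
- Only per-PCI time added (c = 0): 1140 / 3725 = 30.6% at t = 150; 1350 / 4250 = 31.8% at t = 1200.
- Setting the expression equal to 1110 / 3650 gives 730t = 1110c + 555t, so c = (175 / 1110)t, about 0.16t. Above that, the relative saving falls below 30.4%.
- With an assumed 40 common minutes: at 5 EUR per minute (c = 200, t = 150), 1140 / 3925 = 29.0%; at 20 EUR per minute (c = 800, t = 1200), 1350 / 5050 = 26.7%.

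The euro gap widens in all these cases, while the percentage can rise or fall.

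**The case against.** A reader might infer that the bias has a known direction and that the FFR saving is understated on any scale. The documents do not support this. The cost hypothesis is stated as a relative reduction, and Step 5 shows that costing time common to both arms can lower the percentage even as the euro gap grows. Only the absolute difference is probably understated.

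Even that is not certain. The FFR guidance section describes incremental adenosine boluses at least 60 seconds apart, intravenous retesting for borderline values and pull-back for serial stenoses. FD-OCT also needs acquisition and measurement, and the article gives no time for either technique. An average excess of 6 to 12 minutes for FFR cannot be ruled out, though nothing in the text asserts it.

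A reader might also add extra stent-optimisation time for FD-OCT. The FFR arm has its own optimisation steps: repeat FFR, post-dilation and possibly a further stent. The one-third figure in the FD-OCT guidance section comes from the centre's own FD-OCT procedures and has no FFR comparator. No between-arm difference in optimisation time follows, so the point rests on the PCI rates alone.

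Three further objections partly stand:
- The make-up of the 3600 EUR for PCI and the 500 EUR for angiography is not stated. If they already include staff and room, adding time to 1110 EUR counts it twice. They are planning figures, however; the analysis rule excludes time, and the gap dropped from the analysed costs is still 0.20t.
- Hospital days are counted, so part of the cost of a staged admission is captured. Laboratory time is not.
- The exclusion is openly stated, and limiting costs to consumables and stay is a recognisable choice of scope. On the euro scale it probably works against the hypothesis that FFR is cheaper. This defends a narrower scope, but not the reason given for it.

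**Conclusion.** The point holds in a limited form. The stated reason for excluding personnel and laboratory time is at odds with the plan's expected PCI rates. The absolute FD-OCT minus FFR difference is probably understated by about 0.20t per patient: 30 to 240 EUR on the assumed times and prices, against a planned 1110 EUR.

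This rests on the anticipated 50% and 30% PCI rates, on similar time per PCI in both arms, and on FFR assessment not taking 6 to 12 minutes longer on average. The contradiction comes from the document; the size is an assumption. The relative saving may move either way from 30.4%. The expected direction of the result is not reversed, and the primary angina endpoint is unaffected. The correction is worth making because cost is a declared endpoint and the remedy is cheap.

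**What to change.** In the Costs analysis section:
- Delete the assumption that personnel and laboratory time is similar.
- Add a room and staff time cost to the index strategy cost. Use recorded procedure time where available. Otherwise use one fixed mean time per diagnostic procedure and one per PCI session, staged sessions included, multiplied by a single unit cost.
- Report the absolute and the relative difference with and without this cost, for a low and a high unit cost.

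The fallback needs only counts of diagnostic procedures and PCI sessions, which the itemised costing requires anyway. The article does not say that procedure times are recorded, so the fix should not depend on them. The downside is small: mean times and unit cost are assumptions, which is why the range should be shown. Fixed means would also not pick up a difference between FFR and FD-OCT assessment times; recorded times would.

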### Regulatory issues

The study protocol was conceived in September 2012, approved by the Ethical Committee of the Catholic University of the Sacred Heart, Polcilinico A. Gemelli Rome, and registered to clinicaltrial.gov (Reference number NCT01824030). The study will be performed in accordance with the ethical standards of the responsible committees on human experimentation and with the Helsinki Declaration. Each patient willing to participate to the study will sign an informed consent module describing aims of the study, features and risks related to the procedure.

### Sample size calculation for clinical outcome

FFR-based treatment has proven to be superior to standard (based on angiography only) treatment by reducing the occurrence of MACE in the long-term [35]. Yet angina relief (an important determinant of quality of life in patients with ischemic heart disease) was not ameliorated by FFR guidance in a recent trial [7]. Thus, the FORZA trial aims to test if FD-OCT guidance may help to improve the clinical management of patients with ischemic heart disease and inconclusive results at coronary angiography. Since hard clinical endpoints are expected to have low frequency and PCI (especially in patients with good prognosis) is performed with the aim of improving the quality of life by eliminating angina and improving heart function, the occurrence of significant residual angina (<90 score at SAQ angina frequency scale) at 13 months has been considered as the primary endpoint.

For sample size calculations, we focused our attention on the clinical outcome at 13 months (a timepoint chosen assuming that most of patients had completed their 12-month double antiplatelet therapy one month before). Then, based on the FAME trial [7], we anticipate 20% of patients will be suffering from persistent angina at follow up in the FFR guidance group. Thus, 20% of patients are expected to have reached the primary endpoint at 13 months in the FFR guidance group. For the present study, we hypothesize that FD-OCT guidance could be able (due to the treatment of a greater number of stenoses and the optimization of stenting procedures which may reduce the rate of untreated angina-causing lesions) to reduce the occurrence of the primary endpoint by 50%. As a consequence, a total number of 400 patients (200 randomized to FFR guidance and 200 to FD-OCT guidance) has been calculated to be needed with an alpha error of 5% and a beta error of 20%.

This sample size is also suitable to satisfy the secondary endpoint of the study, represented by a combination of MACE and/or relief from angina at 13-month follow up. Indeed we assume to have a 5% rate of MACE in the FFR guidance group, in line with the rate observed in a previous study of patients with intermediate lesions treated on the basis of FFR [10]. Thus, combined with the 20% of patients suffering persistent angina at follow up in the FFR guidance group, 25% of patients are expected to have reached the secondary endpoint at 13 months in the FFR guidance group. Since we expect a significant reduction in angina but not in MACE occurrence in the FD-OCT patients, we assume a 50% reduction (exclusively due to angina relief) of the secondary endpoint in this group. As a consequence, a total number of 304 (152 randomized to FFR guidance and 152 to FD-OCT guidance) has been calculated to satisfy the secondary endpoint requirements, with an alpha error of 5% and a beta error of 20%.

Finally, since the sample size is strongly dependent on the rate of events observed in the reference group (and figures in the literature are highly variable), when the first 150 patients complete the 13-month follow up, an interim analysis will be performed and eventually an amendment with a novel sample sizing will be calculated in the case of >30% difference between expected and observed rates.

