DEFER [6]	2007	325	FFR	Intermediate Stenosis	FFR guided PCI FFR guided OMT	5 years	↔ in PCI vs OMT (3.3% vs 7.9%, *P* = n.s)	↓ in OMT vs PCI (43.0% vs 33.0%, *P* = 0.02)
Courtis *et al.*[10]	2008	107	FFR	Intermediate Stenosis	FFR guided PCI FFR guided OMT	13 months	↓ in PCI vs OMT (5% vs 23%, *P* = 0.005)	↓ in PCI vs OMT (9.0% vs 41.0%, *P* = 0.002)
Courtis *et al.*[11]	2009	142	FFR	Intermediate Stenosis on LM	FFR guided PCI FFR guided OMT	14 months	↔ in PCI vs OMT (7.0% vs 16.0%, *P* = n.s.)	↓ in PCI vs OMT (20.0% vs 36.0%, *P* = 0.008)
Nam *et al.*[12]	2010	167	FFR vs IVUS	Intermediate Stenosis	FFR guided PCI IVUS guided PCI	1 year	↔ in FFR vs IVUS (3.6% vs 3.2%, *P* = n.s.)	________
Muller *et al.*[13]	2011	730	FFR	Intermediate Stenosis on LAD	FFR guided PCI FFR guided OMT	40 months	↓ in OMT vs PCI (9.7% vs 26.7%, *P* <0.001)	________
Misaka *et al.*[14]	2011	44	FFR	Intermediate Stenosis	FFR guided PCI FFR guided OMT	53 months	↔ in PCI vs OMT (13.3% vs 6.9%, *P* = n.s)	________

FFR, fractional flow reserve; FUP, follow up; IVUS, intravascular ultrasound; LAD, left anterior descending; LM, left main; MACE, major cardiovascular event; MI, myocardial infarction; OMT, optimal medical therapy; PCI, percutaneous coronary intervention.

On the other hand, frequency domain technique optical coherence tomography (FD-OCT), an intracoronary imaging technology warranting quick and precise evaluation of coronary lumen and the vessel wall [4], has entered into clinical practice, providing promising clinical results when applied to guide PCI [9]. On such a basis, most of interventional cardiology centers are (or are going to be) equipped with one or both of the equipment for FFR and FD-OCT. Due to the absence of dedicated trials (Table 1) [6,10-14], the decision of when to use one of these two tools is left to the operator and/or centre preference. Yet, these two techniques have a completely different approach to plaque evaluation, since stenosis-related flow limitation and plaque morphology may influence different aspects of the natural history of ischemic heart disease. Thus, we designed the present prospective clinical trial aimed at comparing the clinical and economic implications associated with the selection of FFR or FD-OCT in the management of patients with AICL.

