If an FFR value of >0.80 is measured on the target AICL, patients will be treated with optimal medical therapy only. If an FFR of ≤0.80 is obtained, patients will undergo a FFR-guided PCI. This means that the patient will undergo conventional PCI with stenting of the AICL in order to achieve a post-stenting FFR ≥0.90. If post-stenting FFR is <0.90 a further post-dilation of the stent will be performed, and if FFR remains at <0.90, a pull-back of the wire to identify another possible pressure drop and/or a subsequent stent implantation at least 5 mm from the stent will be performed according to physician’s preference.

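### The 5% MACE rate for the FFR arm is the PCI-group rate of reference 10, which does not support it for an arm expected to be 70% medically treated

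*Protocol article*

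**What the plan says.** All references are to the Protocol article.

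- *Sample size calculation for clinical outcome*, on the first secondary endpoint: "we assume to have a 5% rate of MACE in the FFR guidance group, in line with the rate observed in a previous study" of intermediate lesions managed by FFR, citing reference 10. Angina is set separately: "we anticipate 20% of patients will be suffering from persistent angina at follow up in the FFR guidance group". The two are added, so that "25% of patients are expected to have reached the secondary endpoint at 13 months in the FFR guidance group". This is halved to 12.5% under FD-OCT, with the benefit attributed to angina alone. The result is 304 patients (152 per arm), and the planned 400 are said to cover this endpoint too.
- *Background*, Table 1, row for reference 10 (107 patients, 13 months): MACE is lower "in PCI vs OMT (5% vs 23%, *P* = 0.005"). Both groups are labelled as FFR guided.
- *FFR guidance*: "If an FFR value of >0.80 is measured on the target AICL, patients will be treated with optimal medical therapy only".
- *Sample size calculation for peri-procedural management costs*: "we expect a 30% of PCI in the FFR-guided arm", citing reference 17. For the other arm, "PCI is anticipated to be performed in about 50% of the FD-OCT-guided arm".
- *Study endpoints*: the combined endpoint becomes primary if MACE differs by more than 1 percentage point between arms.

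**The concern.** The FFR arm will contain patients who have PCI and, in larger number, patients deferred to medical therapy. Reference 10 reports both kinds, with very different MACE rates. The plan takes the lower rate, that of the PCI group, and applies it to the whole arm as if the source had observed it there.

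The input feeds the 25% combined rate, the 304 patients and the statement that 400 are enough. The plan expects no MACE difference between arms. Under that premise a higher common MACE rate adds variance without adding signal, so power falls. The combined endpoint can also be promoted to primary, so its power is not a side matter.

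**Working it through.** **1. The plan's own figure.** The pooled-variance formula for two proportions is, per arm,

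n = [1.960·√(2p̄(1−p̄)) + 0.842·√(p₁(1−p₁) + p₂(1−p₂))]² / (p₁−p₂)²

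with two-sided α of 5%, 80% power, 1:1 allocation and no continuity correction. For 25% versus 12.5% it gives 151.9, so 152 per arm and 304 in total, exactly as stated. (Sidedness is not stated; two-sided reproduces the figure.) The arithmetic is sound and the fault lies in an input. The primary calculation, 20% versus 10%, gives 199 per arm against 200 stated and uses no MACE rate.

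**2. What reference 10 gives for a mixed arm.** With w the share having PCI, the arm's rate is w × 5% + (1−w) × 23%.

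| PCI share w | Weighted MACE |
|---|---|
| 20% | 19.4% |
| 30% (the plan, FFR arm) | 0.30 × 5% + 0.70 × 23% = 17.6% |
| 50% (the plan, FD-OCT arm) | 14.0% |
| 70% | 10.4% |
| 100% | 5.0% |

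Only an arm in which every patient has PCI returns 5%. If the two labels in that row were swapped, the 30/70 mix would give 0.30 × 23% + 0.70 × 5% = 10.4%, still not 5%.

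**3. Other rates in the article.** Table 1 gives 3.6% for the FFR arm of the FFR versus IVUS study at 1 year. The *FD-OCT guidance* section gives, for lesions left untreated after a negative FFR, 0.2% MI and 3.2% revascularization in FAME, and 3.3% for the defer group of DEFER. Taking 0.2% + 3.2% = 3.4% for deferred patients and 5% for PCI patients, 0.30 × 5% + 0.70 × 3.4% = 3.9%.

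**4. Combined-endpoint power at 200 per arm.** Keep the plan's premises: MACE equal in both arms, angina 20% versus 10%, and the two rates simply added. Power is Φ[(|p₁−p₂| − 1.960·SE₀)/SE₁], where SE₀ = √(2p̄(1−p̄)/200) and SE₁ = √((p₁(1−p₁)+p₂(1−p₂))/200). For MACE 5%: SE₀ = 0.0400, SE₁ = 0.0397, (0.100 − 0.0784)/0.0397 = 0.544, and Φ = 0.707.

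| MACE, both arms | Composite | Needed per arm for 80% | Power at 200 per arm |
|---|---|---|---|
| 3.6% | 23.6% vs 13.6% | 237 | 73% |
| 5% | 25% vs 15% | 250 | 71% |
| 10% | 30% vs 20% | 294 | 64% |
| 17.6% | 37.6% vs 27.6% | 344 | 57% |

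**5. Separating two causes.** On the plan's 25% versus 12.5%, power at 200 per arm is 90%. It is 71% at 5% MACE because halving angina alone removes 10 points (25% to 15%), not 12.5. That is a separate defect. The MACE input accounts only for movement along the table, from 71% at 5% down to 57% at 17.6%.

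**6. Dropping the equal-MACE premise.** If reference 10's rates follow PCI share in both arms, MACE is 17.6% versus 14.0% and the composite 37.6% versus 24.0%. That needs 180 per arm, with power 84% at 200. If the 50% relative reduction is kept (37.6% versus 18.8%), 89 per arm suffice.

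**7. The switch rule.** With no true MACE difference and 200 per arm, the observed difference exceeds 1 point with probability about 56% at 5% MACE and 74% at 17.6%.

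**The case against.** The strongest reply is that 5% is a reasonable number with a poor citation. The article's own rates for FFR-negative patients are 3.2–3.3%, the FFR versus IVUS study shows 3.6%, and 23% is the highest medical-therapy rate in Table 1 (the others are 16.0%, 9.7%, 7.9% and 6.9%, the last three over 40 months or longer). This largely stands. It has limits: follow-up and endpoint definitions differ, Table 1 labels the 3.6% group as FFR guided PCI, so its share of deferred patients is not shown, and DEFER's 3.3% sits under PCI in Table 1 but under the defer group in the text.

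A reader might infer that reference 10 implies a 17.6% rate, and that the composite therefore has 57% power and needs 688 patients. The documents do not support this. The 30% share comes from reference 17, and reference 10's own split is not shown, nor is the FFR range of its medical group. The 57% also puts 17.6% in both arms; weighting each arm by its own PCI share gives 84%. So 57% is the lower end of a range that holds under the plan's equal-MACE premise.

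It is also fair that the article calls literature rates highly variable and foresees re-sizing after 150 patients if rates differ by more than 30%. But that check does not name MACE, and it does not correct the attribution.

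**Conclusion.** The point holds as a wrongly transferred input, not as an arithmetic error. Reference 10, as tabulated in the article, does not support 5% MACE for an arm expected to be 70% medically treated. This conclusion does not depend on the exact PCI share. It does not show that 5% is wrong as a forecast: the document's figures span about 3.6% to 17.6%, with several near the lower end.

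Over that span, assuming equal MACE, angina 20% versus 10% and no overlap between the components, composite power at 400 patients runs from 73% to 57%, below 80% throughout. At 5% the shortfall belongs to the halving assumption; only the further decline above 5% belongs to this input. The practical weight comes from the rule that can make this endpoint primary. It should be corrected, but it does not threaten the angina-based sample size.

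**What to change.** In *Sample size calculation for clinical outcome*:

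1. Remove the attribution of 5% to reference 10, or rest the rate on the sources in the article that do support about 4–5%, saying how PCI and deferred patients are weighted.
2. State the MACE assumption as a range, about 3.6% to 17.6%.
3. Replace the claims that 304 patients suffice and that 400 also serve the combined endpoint with its power at 200 per arm, assuming equal MACE and angina 20% versus 10%: about 73% at 3.6%, 71% at 5%, 64% at 10% and 57% at 17.6%.
4. Say that the shortfall at 5% comes from the 50% reduction applied to the whole composite, and that power is about 84% if MACE follows PCI share in both arms (17.6% versus 14.0%).
5. Name the pooled MACE rate among the rates checked at the 150-patient interim.

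The cost is restated planning figures and a less favourable statement about the combined endpoint. No patients are added, and the 400 for the primary angina endpoint stays as it is.
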